#### Secondary Analysis: PSQI Changes

The PSQI global score change from baseline (day 0) to follow-up (day 60) is compared between groups using the independent samples *t* test. The correlation between the Samsung score change and PSQI change is calculated using Pearson *r*.

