### Trial Design

This is a parallel-group randomized controlled pilot trial with a 1:1 allocation ratio. Participants are stratified by sex (male/female) and randomized to either (1) a control group receiving generic sleep hygiene education or (2) an experimental group receiving personalized ML-derived behavioral recommendations.

The observation period is 60 days, which aligns with PSQI requirements for 30-day data collection periods. PSQI assessments are performed at (1) baseline (prior to device use), (2) day 30 (first monitoring period), and (3) day 60 (postintervention period). This enables subjective-objective correlation while establishing a baseline (days 1‐30) to be used as a covariate for intervention analysis (days 31‐60). While 30 days may be minimal for entrenching behavior change, this pilot will establish feasibility and preliminary effect sizes for future extended trials.

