### Interventions

#### Control Intervention: Generic Sleep Hygiene Education

Control group participants receive standardized sleep hygiene education on day 30, covering general recommendations applicable to all adults. Examples include maintaining a consistent sleep-wake schedule and sleeping between 7 and 9 hours per night. These recommendations are not personalized to individual sleep patterns.

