### Intervention Delivery and Verification

Experimental group participants receive personalized recommendations explained by the researcher in person on day 30. Participants can clarify and provide feedback. A closure interview at day 60 verifies engagement and implementation attempts, and includes a subjective effectiveness assessment.

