#### Exploratory Analyses: Hypothesis Generation Only

The exploratory analyses involve the following three aspects:

Individual parameter changes: Compare the change in specific sleep variables (duration, deep sleep percentage, and REM percentage) between groups using *t* tests (unadjusted for multiple comparisons, given the exploratory nature).Adherence subgroups: In the experimental group, compare outcomes between high (≥80%) and low (<80%) self-reported adherence using the Mann-Whitney *U* test.Predictive feature patterns: Perform a descriptive analysis of which sleep parameters are most frequently identified as the top predictors across participants.

All exploratory analyses are labeled hypothesis-generating, not confirmatory. No adjustments are made for multiple comparisons, given the pilot scope of the study. Regarding the handling of missing data for the primary outcome (sleep score), participants are excluded if sufficient night data are not available in the baseline and postintervention periods, and action on the secondary outcome (PSQI) is derived from the handling of the primary outcome. This protocol contains the complete statistical analysis plan, and no separate statistical analysis plan exists.

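### As written, the validation correlation pairs a score change and a PSQI change with different starting months, and the day-30 PSQI enters no stated analysis; the between-group PSQI test is valid but inefficient

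*Protocol article*

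**What the plan says.** The Trial Design section of the protocol article sets the schedule: "PSQI assessments are performed at (1) baseline (prior to device use), (2) day 30 (first monitoring period), and (3) day 60 (postintervention period"). It says that the 60-day observation period "aligns with PSQI requirements for 30-day data collection periods" and gives the purpose: "This enables subjective-objective correlation while establishing a baseline" over days 1–30, which then serves as covariate for days 31–60.

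Both arms are treated on the same day. "Experimental group participants receive personalized recommendations explained by the researcher in person on day 30", and "Control group participants receive standardized sleep hygiene education on day 30".

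The primary analysis is an ANCOVA of the mean score over days 31–60 on the mean score over days 1–30. For the PSQI, the Secondary Analysis section says: "The PSQI global score change from baseline (day 0) to follow-up (day 60) is compared between groups using the independent samples" *t* test. The next sentence reads: "The correlation between the Samsung score change and PSQI change is calculated using Pearson" *r*. No other PSQI change is defined, and the score change is not defined at all. The exploratory section uses the same change-score form: "Compare the change in specific sleep variables (duration, deep sleep percentage, and REM percentage) between groups", by *t* tests.

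The exploratory section closes by saying that the protocol holds the whole statistical analysis plan and that there is no separate one. The point therefore cannot be deferred to another document.

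**The concern.** The outcome sections give the PSQI a specific job: to show that gains in a proprietary score, whose composite has no polysomnography validation, match what participants perceive. The correlation of changes is the analysis that does this. If its two changes start from different months, part of the PSQI change reflects a period with no score to compare it with. A weak r could then be read as failed validation when part of the weakness comes from the windows. The form that would match the windows is collected and left unused.

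The second issue is precision. With 32 participants, and an interpretation section that rests on effect sizes and their intervals, an unadjusted change score gives up precision that the plan already secures for its primary outcome.

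**Working it through.** **Inputs.** From the protocol: PSQI on days 0, 30 and 60 with 30-day periods; both interventions on day 30; score windows of days 1–30 and 31–60; 16 per arm. The documents give no PSQI standard deviation, reliability or correlation over time, so every such value below is an assumption.

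**The plan's own figure.** The only power statement is above 80% for d≥1.0. With 16 per arm and the one-sided 0.05 level stated for the primary analysis, noncentral-*t* power is 86.8%, so it reproduces (two-sided: 78.1%). No figure is given for the PSQI.

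**Step 1: windows side by side.**

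| Quantity | Starts from | Ends with |
|---|---|---|
| Score change (inferred; no score before day 1) | days 1–30 | days 31–60 |
| PSQI change as written | month before device (day-0 form) | days 31–60 (day-60 form) |
| PSQI change available but unused | days 1–30 (day-30 form) | days 31–60 (day-60 form) |

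**Step 2: effect on r (sizes without sign).** In the limiting case of perfect measures and independent monthly fluctuations e0, e1, e2, the score change is e2−e1 and the PSQI change is e2−e0 up to sign. The covariance is 1 and each variance is 2, so r = 1/2. Matched windows give 1.0.

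A less extreme model lets monthly sleep quality follow a first-order autoregression with correlation a. The score's noise variance is s = 0.1/0.9 (reliability 0.9) and the PSQI's is p = (1−reliability)/reliability.

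- Matched: r = 2(1−a) / √{[2(1−a)+2s][2(1−a)+2p]}
- As written: r = (1−a²) / √{[2(1−a)+2s][2(1−a²)+2p]}

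For a = 0.7 and PSQI reliability 0.8 (p = 0.25): matched 0.60/√(0.822×1.10) = 0.63; as written 0.51/√(0.822×1.52) = 0.46. Simulation of the same model gave:

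| a | PSQI reliability | Matched | As written | Loss |
|---|---|---|---|---|
| 0.50 | 0.6 | 0.591 | 0.402 | 0.189 |
| 0.50 | 0.8 | 0.739 | 0.479 | 0.260 |
| 0.70 | 0.6 | 0.475 | 0.366 | 0.109 |
| 0.70 | 0.8 | 0.633 | 0.456 | 0.177 |
| 0.85 | 0.6 | 0.324 | 0.279 | 0.045 |
| 0.85 | 0.8 | 0.465 | 0.375 | 0.090 |

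**Step 3: is the between-group test biased?** Simulation used 16 per arm, a true effect of −0.50 SD, a shift common to both arms from the first month of wear, rho(0,60) = 0.5 and rho(30,60) = 0.7. The day 0–60 change gave −0.499 (SE 0.355) and the day 30–60 change −0.500 (SE 0.275). Neither is biased. The SEs agree with √(2v/16): 0.354 at v = 1.00 and 0.274 at v = 0.60.

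**Step 4: efficiency, with the two gains kept apart.** In units of PSQI variance, assumed equal over time, raw change has variance 2(1−rho) and ANCOVA 1−rho². At the same rho the ratio is (1+rho)/2: 0.75 at rho 0.5 and 0.85 at rho 0.7. That gain needs no change of window.

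The window matters only if the two correlations differ. With rho(0,60) = 0.50 and rho(30,60) = 0.65, raw change gives 2(1−0.50) = 1.00, ANCOVA on day 0 gives 1−0.25 = 0.75, and ANCOVA on day 30 gives 1−0.4225 = 0.58. The window's own share is 0.5775/0.75 = 0.77, a 23% reduction.

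Approximate power at d = 0.7 PSQI SD, 16 per arm, two-sided 0.05:

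| rho(0,60), rho(30,60) | Raw change 0–60 | ANCOVA on day 0 | ANCOVA on day 30 |
|---|---|---|---|
| 0.4, 0.6 | 42% | 55% | 67% |
| 0.5, 0.7 | 48% | 60% | 77% |
| 0.7, 0.7 | 70% | 77% | 77% |
| 0.7, 0.85 | 70% | 77% | 95% |

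**The case against.** **Day 0 is a legitimate baseline.** The protocol labels it the PSQI baseline, and allocation is revealed only after that form is completed. A reader might infer that the between-group test uses a wrong baseline or gives a biased answer. The documents do not support that: randomisation protects the contrast, and Step 3 shows no bias. This objection stands in full.

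**The extra 30 days need not cost anything.** A reader might say that the untreated month only adds noise. That holds only if day 0 predicts day 60 less well than day 30 does. This is plausible, but no document figure shows it, and with equal correlations the window makes no difference. Nor may the combined 0.58 be quoted as the price of the day-0 window, since the move to ANCOVA accounts for the step from 1.00 to 0.75.

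**The correlation window is inferred.** The sentence on the correlation names no window; day 0 to day 60 carries over from the sentence before. The Study Uniqueness section refers to a 30-day correlation framework, so matched windows may be intended. This limits the charge to what the text says as written; the text still needs correcting.

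**Sampling error is larger than the attenuation.** The half-width on Fisher's z scale with 32 people is 1.96/√29 = 0.364, so r = 0.63 has an interval of about 0.36 to 0.80 and r = 0.46 one of about 0.13 to 0.70. That is true, but the attenuation is systematic and costs nothing to remove.

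**The day-30 form is post-randomisation and falls on the day of delivery.** The measurement schedule lists the PSQI first but does not fix the order. This stands as a condition on the fix. The primary covariate, days 1–30, is also post-randomisation.

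**It is a pilot.** This carries weight for the exploratory variables, which are labelled hypothesis-generating. It carries less for the PSQI, because the pilot's stated value includes estimating effect sizes.

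**Conclusion.** The point holds in two parts of unequal weight.

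The main part is the correlation. As written, its two changes start from different months, against the schedule's stated purpose, and the matching day-30 form is unused. The expected effect is a weaker r: a loss of about 0.04 to 0.26 over the assumed range (month-to-month correlation 0.5 to 0.85, PSQI reliability 0.6 to 0.8, score reliability 0.9). The drop from 1.0 to 0.5 is a limiting case and should not be quoted as the expected size.

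The lesser part is the between-group test, which is valid and unbiased but inefficient. The gain from ANCOVA follows for any correlation below 1, with size (1+rho)/2 under equal variances. The further gain from a day-30 covariate depends on correlations that the documents do not give, and may be nil.

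**What to change.** - Define the score change as the mean over days 31–60 minus the mean over days 1–30, and correlate it with PSQI change from day 30 to day 60.
- Analyse day-60 PSQI by ANCOVA on group with day-30 PSQI as the single covariate. Repeat with day-0 PSQI as the covariate as a sensitivity analysis.
- State that the day-30 PSQI is completed before group assignment is disclosed and the intervention delivered. Where that order was not kept or cannot be confirmed, report it and give weight to the day-0 analysis.
- Using ANCOVA for the exploratory sleep variables is optional.

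The cost is wording. All three forms are already in the schedule, and one covariate is what the plan accepts for its primary model. The change should be dated and recorded before outcomes are analysed, which the protocol says happens only after study completion.

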#### Exploratory Analyses: Hypothesis Generation Only

The exploratory analyses involve the following three aspects:

Individual parameter changes: Compare the change in specific sleep variables (duration, deep sleep percentage, and REM percentage) between groups using *t* tests (unadjusted for multiple comparisons, given the exploratory nature).Adherence subgroups: In the experimental group, compare outcomes between high (≥80%) and low (<80%) self-reported adherence using the Mann-Whitney *U* test.Predictive feature patterns: Perform a descriptive analysis of which sleep parameters are most frequently identified as the top predictors across participants.

All exploratory analyses are labeled hypothesis-generating, not confirmatory. No adjustments are made for multiple comparisons, given the pilot scope of the study. Regarding the handling of missing data for the primary outcome (sleep score), participants are excluded if sufficient night data are not available in the baseline and postintervention periods, and action on the secondary outcome (PSQI) is derived from the handling of the primary outcome. This protocol contains the complete statistical analysis plan, and no separate statistical analysis plan exists.

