### Sleep Quantity

Sleep quantity refers to the amount of daily time spent sleeping (sleep duration), measured in hour units. The American Academy of Sleep Medicine, the Sleep Research Society, and the National Sleep Foundation agree that adults (aged 18‐60 years) need a minimum of 7 hours of sleep each night [87,88], and a sleep duration less than that implies a sleep deprivation condition (insufficient sleep) [18]. The following variables can be considered for assessment: (1) time in bed (TIB), period from lights off to lights on; (2) total sleep time (TST), actual time spent sleeping (sleep quantity) consistently shorter than TIB unless efficiency reaches 100%; and (3) sleep efficiency ([TST / TIB] × 100).

There are four main disadvantages of relying on this metric in isolation: (1) quantity increase does not guarantee a positive correlation with sleep quality (eg, during the 2021 pandemic period, Americans were sleeping more [quantity], but sleep quality declined) [89]; (2) TIB can be misunderstood as TST (these are only equal if 100% sleep efficiency is achieved) [90-92]; (3) sleeping beyond a limit can have negative consequences, such as stroke [93] and intracerebral hemorrhage [94] (the National Sleep Foundation has recommended a maximum sleep duration of 9 hours [88]); and (4) sleeping time cannot provide valuable data on sleep architecture, including time spent in each of the 4 sleep stages, number of sleep cycles, distribution of sleep stages, and transition speed between sleep phases [90-92].

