### Personalized Sleep Intervention Framework

The intervention content is based on individual ML feature importance ranking, and participants receive nonpharmacological recommendations from a predefined library (Multimedia Appendix 1) targeting their top 2‐4 predictive sleep parameters [108-116]. Example recommendations for TST optimization (if sleep_duration is a key predictor) are as follows: ensure wake-up time commitment for too much sleep and bedtime commitment for too little sleep. Example recommendations for sleep efficiency enhancement (if movement_awakening is a predictor) are as follows: use white noise, ensure a quiet environment, and restrict caffeine intake (avoid intake ≤6 hours before bedtime). Example recommendations for sleep timing regulation (if sleep_cycle is a predictor) are as follows: ensure a consistent sleep-wake schedule and keep the bedroom cool (around 18 °C‐20 °C).

Experimental group participants receive personalized recommendations, and the top 2‐4 recommendations are explained by the researcher during the in-person meeting. Adherence tracking involves self-reported compliance assessed at study closure (0%‐100% scale). Control group participants receive generic sleep hygiene education without personalization by the researcher during the in-person meeting.

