### Exploratory Outcomes

The exploratory outcomes include (1) individual sleep parameter changes (which specific variables improve), (2) adherence to personalized recommendations (self-reported 0%‐100% scale), and (3) behavioral confounders (alcohol consumption, exercise, and stress documented in the closure interview).

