### Data Collection Quality Control

The following measures are implemented for user-related issues: (1) noncompliance: participants with missing data for >20% of nights are excluded and replaced; (2) charging issues: backup chargers are provided, and daily battery monitoring is required; (3) unauthorized modifications: settings are locked, and violations lead to replacement; and (4) sync delays: daily commitment for cloud backup within 24 hours. The following measures are implemented for device-related issues: (1) fragmented recording: nights without combined scores are excluded; (2) data mismatch: nights with artifact conflicts are excluded; and (3) sync errors: multiple attempts are made with escalating intervals. For sensor inaccuracies, quality control is performed through sleep diaries, and outliers trigger replacement. Excluded participants are replaced from the recruitment pool to maintain the sample size. The expected night exclusion impact is around 18%, with anticipated replacement ensuring the target sample.

Subjective data collection is performed through PSQI forms completed on paper. Information is manually entered by the researcher into a password-protected spreadsheet with self-verification (data are entered twice by the researcher to ensure accuracy). Data are processed through the manufacturer’s algorithms to interpret the findings of the 10 explanatory variables and the target variable (Table 1).

**Table 1. T1:** Target and explanatory variables collected by the wearable (indispensable for this study).

Variable		Description	Unit	Data type
Explanatory variable				
sleep_duration		Sum of N1, N2, N3, and REM^a^	Minutes	Integer
movement_awakening		Count of movement during sleep	Number	Integer
sleep_cycle		Count of sleep cycles	Number	Integer
mental_recovery		Score assigned according to the REM phase	Score (0‐100 scale)	Integer
physical_recovery		Score assigned according to the N3 phase	Score (0‐100 scale)	Integer
efficiency		real_total_sleep by sleep_duration	Percentage	Integer
Transition_N1		Sum of minutes of sleep in the N1 phase	Minutes	Integer
Light_N2		Sum of minutes of sleep in the N2 phase	Minutes	Integer
Deep_N3		Sum of minutes of sleep in the N3 phase	Minutes	Integer
REM		Sum of minutes of sleep in the REM phase	Minutes	Integer
Target variable				
sleep_score		Score assigned for the night	Score (1‐100 scale)	Integer

a REM: rapid eye movement.

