### Accountability Framework

The accountability framework involves the following aspects:

Adverse events from artificial intelligence (AI): If ML-derived recommendations cause participant harm (eg, a recommendation to reduce sleep duration leads to excessive daytime sleepiness affecting work safety), the event is documented as an adverse event. The researcher notifies the ethics committee, and an investigation is conducted to determine if a systematic model error exists.Replication and audit: The ML code, trained models, and analysis scripts are made available to the ethics committee and peer reviewers upon request.Model performance monitoring: During the study, the principal researcher monitors whether the experimental group shows unexpected negative outcomes (eg, worsening sleep scores), triggering a review of ML recommendation patterns for systematic errors.

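### The exploratory test of sleep duration measures average lengthening, not improvement, so gains by short and long sleepers offset each other (minor)

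*Protocol article*

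**What the plan says.** Exploratory Outcomes gives the purpose as "individual sleep parameter changes (which specific variables improve"). The matching item under Exploratory Analyses is to "Compare the change in specific sleep variables (duration, deep sleep percentage, and REM percentage) between groups", using t tests without adjustment for multiplicity. Table 1 (Data Collection Quality Control) defines sleep_duration as "Sum of N1, N2, N3, and REM", in minutes. Neither Table 1 nor Table 2 contains a target or a distance-to-target version.

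The advice on duration has two directions. The example in Personalized Sleep Intervention Framework, for participants whose model ranks sleep_duration as a key predictor, is to "ensure wake-up time commitment for too much sleep and bedtime commitment for too little sleep". Accountability Framework gives, as an example of possible harm, "a recommendation to reduce sleep duration leads to excessive daytime sleepiness affecting work safety". Control participants are told about "sleeping between 7 and 9 hours per night". Sleep Quantity gives a 7-hour minimum and a 9-hour recommended maximum, and warns that "sleeping beyond a limit can have negative consequences".

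The protocol states that it holds the whole statistical analysis plan and that no separate one exists.

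**The concern.** For sleep duration, higher is not always better on the protocol's own account. A t test on change in minutes has as its null hypothesis that the two arms lengthen sleep equally on average. A long sleeper who comes down toward 9 hours enters as a negative change and offsets a short sleeper who comes up toward 7 hours. A participant who drifts beyond 9 hours enters as a gain. The comparison therefore does not answer whether duration improved.

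The offset is in the effect estimate itself, not only in the p-value, so reporting effect sizes and confidence intervals does not remove it. The pilot is meant to supply effect sizes (Pilot Objectives) and to show which sleep parameters respond most reliably to personalization (Implications for Future Research). A partly cancelled duration effect would enter that choice.

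**Working it through.** **1. The plan's own figure.** The text gives no power for the duration test. The only stated power is above 80% for d ≥ 1.0 with 16 per arm. The noncentrality is 1 × √(16/2) = 2.83 with 30 degrees of freedom. The t-test power is 86.8% one-sided at .05 and 78.1% two-sided. The stated figure reproduces with the one-sided alpha of the primary analysis. Sidedness of the exploratory t tests is not stated, so two-sided .05 is used below.

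**2. How the offset arises.** The range is 7 × 60 = 420 to 9 × 60 = 540 minutes. Take two participants: 390 → 420 (+30) and 570 → 540 (−30). The mean signed change is (30 − 30)/2 = 0. Distance from the range falls from 30 to 0 in both.

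**3. General form.** If all participants shift by D in their advised direction and a share q lengthens, the mean signed change is qD − (1−q)D = D(2q−1). The power column is from 40,000 simulated trials per row, with D = 1 SD of change in every experimental participant and no shift in controls.

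| Lengthen : shorten (of 16) | q | Mean signed change | Power, signed t test | Power, change signed toward target |
|---|---|---|---|---|
| 16 : 0 | 1 | 1.00 D | 78% | 78% |
| 14 : 2 | 0.875 | 0.75 D | 45% | 78% |
| 12 : 4 | 0.75 | 0.50 D | 17% | 78% |
| 10 : 6 | 0.625 | 0.25 D | 4% | 78% |
| 8 : 8 | 0.5 | 0 | 2% | 78% |

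Power falls below 5% in the last rows because opposite shifts also inflate the within-arm variance.

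**4. A case closer to the trial.** Some participants are already in range. With a share s below 7 hours and a share l above 9 hours, the arm's mean signed shift is D(s−l) under full response, and the mean shift toward the range is D(s+l). The documents give 35% to 40% of Mexican adults below 7 hours and no figure above 9 hours. Take D = 30 minutes and s = 40% (D and l are assumptions):

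- l = 0: signed 30 × 0.4 = 12 min; toward range 12 min.
- l = 10%: signed 30 × 0.3 = 9 min; toward range 15 min.
- l = 20%: signed 30 × 0.2 = 6 min; toward range 18 min.

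**5. Response rate.** For s = 40% and l = 10%, the signed difference between arms is 9 minutes times the difference in response rates. The simulation assumes 25 usable nights per period, night SD 50 minutes, extra period SD 10 minutes, and a spread of habitual sleep times that the documents do not give.

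| Responders, experimental / control | Signed difference | Signed t test | Distance from range, baseline-adjusted |
|---|---|---|---|
| 100% / 0% | 9 min | 19% | 66% |
| 50% / 0% | 9 × 0.5 = 4.5 min | 9% | 18% |
| 70% / 30% | 9 × 0.4 = 3.6 min | 9% | 13% |

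The distance analysis kept a type I error of about 5% and was not materially worse than the signed test in any mix tried.

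**The case against.** The strongest reply concerns size. Only participants whose model ranks sleep_duration as a key predictor get the advice, and controls are also pointed to 7 to 9 hours, so the first row of the last table is a best case. Offsetting also needs a real share of people above 9 hours. The sample is full-time workers in a city described by long commutes and shift work, and the variable is minutes asleep, not time in bed. That share may be small. All of this stands. It means the loss cannot be quantified from the documents, and that the distance measure would not make this comparison well powered.

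A reader might infer that the pilot would report that duration did not improve. The documents do not support that. Interpretation Guidance commits to effect sizes, intervals and descriptive patterns and disclaims claims of lack of efficacy, and the analysis is labelled hypothesis-generating. A reader might also extend the point to deep sleep and REM percentages. No two-way advice is documented for them.

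Two replies do not hold. The planned descriptive contrast of duration-focused with architecture-focused advice does not separate lengthening from shortening. The exploratory label does not change which quantity is estimated.

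On the remedy, the framework section does not define too much or too little sleep as outside 7 to 9 hours, and the recommendation library is not shown. Distance from the range is skewed, with zero for every night inside it, and ignores changes there. Mean signed change is still useful and should be kept.

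**Conclusion.** The mismatch is real: the outcome asks whether duration improves, and the test asks whether sleep lengthens on average. To the extent that both short and long sleepers are enrolled and respond, their improvements offset each other, by the factor 2q−1 when all shift equally. A near-zero estimate would then not show that duration failed to move toward the protocol's own range.

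How much is lost is unknown. A gap such as 19% against 66% power rests on every out-of-range experimental participant responding and no control responding. Under the partial response assumed above, both analyses stay below 20%. The primary sleep-score analysis of covariance and the PSQI comparison are untouched. This is a minor point, worth correcting because it costs little.

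**What to change.** Under Exploratory Analyses, add for sleep_duration the mean nightly distance from the 7 to 9 hour range that the protocol already cites: max(0, 420 − minutes) + max(0, minutes − 540), averaged over usable nights in each period. Compare arms on the days 31 to 60 value, adjusted for the days 1 to 30 value. Name this as the analysis that answers whether duration improved. Keep mean signed change beside it, described as average lengthening or shortening. Report by arm how many participants had a baseline mean below 7 hours and how many above 9 hours, so that readers can judge the scope for offsetting.

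The cost is one derived variable from data already collected and a sentence or two of analysis text. The downside is that the new variable is skewed and does not register movement inside the range, which is why signed change stays in the report.
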